### Sample size

This exploratory trial was primarily designed to estimate effect sizes and assess protocol feasibility. Consistent with pilot-trial recommendations for acupuncture and traditional Chinese medicine (22, 23), we set the target sample size at 30 participants per arm. Allowing for an anticipated 20% attrition, we therefore planned to enroll 36 participants in each group (total *n* = 72). For the MRI substudy, we will randomly select 15 participants per arm (*n* = 30) from the clinical cohorts, in line with Desmond and Glover’s guidance on imaging sample sizes (24). Under a two-tailed *α* = 0.05, this total sample provides approximately 80% power to detect medium-to-large correlations (r ≥ 0.50) between QSM-derived susceptibility measures and cognitive outcomes, based on Fisher’s z transformation in G*Power 3.1. Smaller associations will be interpreted with caution, and the MRI substudy is therefore primarily intended to provide preliminary estimates of effect sizes and variance components to guide the design of future, adequately powered imaging trials. With 15 participants per arm, the substudy will also have approximately 80% power to detect between-group differences in 4-week changes in regional susceptibility of approximately 0.8 standard deviations (Cohen’s d), whereas smaller treatment effects on QSM will be treated as exploratory and described descriptively.

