Statistical analysis will be performed in SPSS 26.0 (IBM, Armonk, NY, USA). Within-group changes in susceptibility (post–pre) are tested with paired-samples *t*-tests, and between-group differences are assessed with independent-samples t-tests. Pearson correlation coefficients will be calculated to examine associations between changes in ROI-based susceptibility and corresponding changes in cognitive, functional, emotional, and sleep measures; if normality is violated for either variable, Spearman’s rank correlation will be used. Data normality will be assessed with the Shapiro–Wilk test. Two-sided *p*-values of < 0.05 will be considered statistically significant, and false-discovery-rate correction will be applied across the predefined ROIs to control for type I error. Given the 4-week interval and modest imaging sample size, the QSM substudy is not powered to detect small absolute susceptibility changes. We will therefore focus on within-subject changes in ROI-based susceptibility and on medium-to-large associations with cognitive outcomes, interpreting all imaging findings as exploratory.

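### MRI substudy: 15 per arm gives about 56% power, not about 80%, for a 0.8 SD between-group difference in susceptibility change

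*Protocol article*

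**What the plan says.** The Sample size section of the protocol article makes two power statements for the MRI substudy, for which "we will randomly select 15 participants per arm".

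- **Correlations.** "Under a two-tailed *α* = 0.05", the 30 participants together are said to give about 80% power for correlations of 0.50 or more between QSM measures and cognition, using Fisher's z.
- **Group comparison.** For the same 15 per arm it claims that "the substudy will also have approximately 80% power to detect between-group differences in 4-week changes in regional susceptibility of approximately 0.8 standard deviations". Effects smaller than this are to be regarded as exploratory and only described.

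The Neuroimaging data analysis section names an independent-samples t-test for between-group differences and sets significance at a two-sided p below 0.05. It adds that "false-discovery-rate correction will be applied across the predefined ROIs to control for type I error". It lists eight bilateral structures as regions of interest.

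The 20% attrition allowance in the Sample size section takes the clinical sample from 30 to 36 per arm. No allowance is stated for the 15 per arm in the substudy. The MRI data acquisition section provides for excluding scans that are unusable and cannot be repeated.

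**The concern.** The group-comparison statement gives sample size, effect size and power together, and the analysis section supplies the test and the significance level. The claim can therefore be checked directly, and these inputs do not fit together. Fifteen per arm is well short of what a two-sample comparison needs for 80% power at 0.8 SD.

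The statement also has a function in the plan. It sets 0.8 SD as the boundary between treatment effects on QSM that the substudy is said to be able to detect and those that are only described. If the power at that boundary is much lower than stated, a non-significant comparison carries less information about a 0.8 SD effect than the protocol tells its reader.

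**Working it through.** **Inputs**

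- n = 15 per arm, d = 0.8 on the SD of the 4-week change, stated power about 80%: Sample size section.
- Independent-samples t-test, two-sided 0.05: Neuroimaging data analysis section. The power sentence does not repeat the significance level, so a one-sided test is checked as well.

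**Attempt to reproduce the stated 80%**

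Noncentrality = d × √(n/2) = 0.8 × √7.5 = 2.19, with 15 + 15 − 2 = 28 degrees of freedom.

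Normal approximation, two-sided: Φ(2.19 − 1.96) = Φ(0.23) = 59.1%. The exact value comes from the noncentral t distribution.

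| Calculation, 15 per arm, d = 0.8 | Power |
|---|---|
| t-test, two-sided 0.05 (as planned) | 56.2% |
| Normal approximation, two-sided | 59.1% |
| t-test, one-sided 0.05 | 68.9% |
| Normal approximation, one-sided | 70.7% |

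None of these between-group calculations comes near 80%.

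**What 80% would require (t-test, two-sided 0.05)**

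- At 15 per arm: d = 1.06.
- At d = 0.8: 26 per arm (power 80.7%). The normal approximation gives 25: 2 × (1.96 + 0.84)² / 0.8² = 24.5, rounded up.

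**Companion statement on correlations**

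r = 0.50, n = 30, Fisher's z: 0.549 × √27 = 2.854, and Φ(2.854 − 1.96) = 81.4%. This reproduces.

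**Further reductions (illustrations only)**

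- *Loss of scan pairs.* Assume the clinical cohort's 20% attrition also applies to the substudy: 15 × 0.8 = 12 per arm. Power at d = 0.8 is then 46.6%, and 80% power needs d = 1.20. At 13 and 14 per arm, power is 49.9% and 53.1%.
- *False-discovery-rate correction.* The Benjamini-Hochberg procedure at 0.05 was simulated with 4,000 runs per scenario and a correlation between regions of 0 or 0.5. At 15 per arm and d = 0.8, power per affected region runs from about 25% (one of eight regions affected) to about 45% (all eight). With 16 regions, left and right counted separately, it runs from about 19% to 42%. The document gives neither the number of affected regions nor their correlation.

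**The case against.** The strongest defence is that little depends on this figure. The trial is presented as a pilot meant to estimate effect sizes and feasibility. The substudy size is attributed to published guidance on imaging samples, not derived from d = 0.8. The analysis section disclaims power for small absolute susceptibility changes and treats all imaging findings as exploratory. All of that stands and limits the consequence. It does not make the figure right, because 0.8 SD is offered as an effect the substudy can detect and serves as a dividing line.

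A second defence is that baseline adjustment could recover the power. Reaching 80% at 15 per arm would need covariates explaining about 1 − (0.8/1.06)² = 43% of the variance of the change. The imaging section specifies an unadjusted t-test, so this does not rescue the statement.

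A reader might also infer more than the document supports:

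- *That the correlation claim is wrong too.* It is correct at its stated level. Quoting power before multiplicity correction is conventional.
- *That true power is known to be 47% or lower.* The document does not say when the 15 are drawn, whether they are replaced, or how many scans will be lost. If 15 means analysable participants, the attrition point falls away and 56% remains.
- *That the detectable effect under the correction is about 1.4 to 1.5 SD.* Those values come from testing at 0.05/8 or 0.05/16, a worst-case bound and not typical false-discovery-rate performance.
- *That the wrong figure is meant to guide later trials.* The Sample size section gives that role to the effect-size and variance estimates the substudy will produce.
- *That a within-group calculation was reported by mistake.* A paired t-test with n = 15 and d = 0.8 does give 82.1%, but nothing in the document shows that this is where the 80% came from.

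**Conclusion.** The power statement for the group comparison is wrong as written. Under the planned test, power at 15 per arm and d = 0.8 is about 56%, some 24 points below the stated figure. A true 0.8 SD effect would be missed about 44% of the time even with every scan pair usable and no multiplicity correction. The result needs no assumption beyond the document's own inputs, and a one-sided reading does not change the conclusion.

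Losses and the false-discovery-rate correction act in the same direction, but their size cannot be fixed from the document. A reader might infer that a null QSM result would be taken as ruling out a 0.8 SD effect. The exploratory labelling does not support so strong a consequence. The primary endpoint, the planned tests and the sample size are unaffected. This is a clear error that should be corrected, with limited reach.

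**What to change.** In the Sample size section, replace the group-comparison power statement with: *With 15 analysable participants per arm the substudy has about 56% power for d = 0.8 and 80% power for d of about 1.06, before FDR correction.* Move the line between powered and descriptive effects from 0.8 SD to match. In the text shown, that line appears only in this section.

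It would help to add that unusable or missing scan pairs lower power further. If 12 per arm is given as an illustration (47% at d = 0.8, 80% at d of about 1.20), the 20% loss should be labelled an assumption. The correlation statement needs no change.

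The cost is wording only: no extra participants or scans and no change to any analysis. The stated power becomes less favourable.

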### Randomization and blinding

Participants will be randomly assigned to either the EA group or the sEA group using a random number table. The randomization sequence will be prepared in advance by an independent investigator who is not involved in participant enrolment, treatment, or outcome assessment. Allocation will be concealed using sequentially numbered, opaque, and tamper-evident envelopes. After confirming eligibility and completing baseline assessments, the treating acupuncturist will open the next envelope in sequence to determine group allocation and initiate the assigned intervention.

Due to the nature of the intervention, blinding treatment providers is not feasible. Therefore, a single-blind design will be used. Participants and outcome assessors will remain blinded to group allocation, while acupuncturists will be aware of treatment assignment but restricted to intervention delivery only. Data entry and statistical analysis will be performed by an independent third party to minimize bias.

To assess the credibility of blinding, we will adopt a procedure similar to that used in recent acupuncture RCTs (25). At the end of the 4-week intervention, participants will be asked to indicate which treatment they believe they have received (EA, sEA, or uncertain). The distribution of responses will be summarized descriptively to evaluate the success of blinding. Based on the Patients’ Expectancy Scale of Acupuncture (PESA) (26), we will include a brief expectancy questionnaire at baseline, asking participants to rate, on a 5-point Likert scale, how much they believe acupuncture will help their post-stroke cognitive recovery.

### Intervention and grouping

Participants will be randomly assigned to either the EA group or the sEA group. All participants will continue standard pharmacotherapy and rehabilitation during the study. Each participant will receive 20 treatment sessions (5 sessions per week for 4 weeks), each lasting 30 min.

#### EA group

Participants in the EA group will receive verum stimulation at Baihui (GV20), Sishencong (EX-HN1), Shenting (GV24), and bilateral Neiguan (PC6), along with five adjunct points—Hegu (LI4), Zusanli (ST36), Xuanzhong (GB39), Sanyinjiao (SP6), and Taichong (LR3)—on the affected side. Three adjunct points will be selected per session based on clinical presentation. Acupoint locations will follow the WHO Standard Acupuncture Point Locations (see Figure 2; Supplementary Table S1).

**Figure 2 fig2:**
[figure not shown]
Location of acupoints and non-acupoints.

After skin disinfection with 75% ethanol, sterile disposable stainless-steel filiform needles (0.25 mm × 40 mm) will be inserted. For scalp points (GV20, EX-HN1, GV24), needles will be inserted obliquely at a 15° angle to the scalp to reach the subgaleal layer, then advanced without rotation to a depth of 0.8 cun. For body points, insertion will follow standard depth and angle: PC6, LI4, ST36, and SP6 will be needled perpendicularly to a depth of 1.0 cun; GB39 perpendicularly to 0.8 cun; and LR3 obliquely to 0.8 cun. A balanced reinforcing–reducing technique will be applied to elicit the deqi sensation. EA will be delivered using the Hua Tuo SDZ-III device with four electrode pairs (GV20–GV24, left–right EX-HN1, and bilateral PC6 with auxiliary needles). Alternating sparse-dense waveforms (2 Hz/10 Hz) will be applied, with stimulation intensity set at 1–2 mA depending on patient tolerance. Identical procedures and device cues were maintained across groups to preserve blinding, while the absence of electrical output in the sEA group ensured inert stimulation.

#### sEA group

Participants in the sEA group will receive sham acupuncture at non-acupoint, non-meridian locations situated 1–2 cun away from the true acupoints. Locations will follow the SHARE guidelines (27) and the relevant systematic review (28), with locations specified in Figure 2 and Supplementary Table S2. Needles (0.25 mm × 25 mm) will be inserted subcutaneously (scalp) or perpendicularly (body) to 0.3 cun, without manipulation or deqi. Electrodes will be placed in the same configuration as in the EA group. To maintain participant blinding, the Hua Tuo SDZ-III device will appear fully operational, with power indicators and auditory signals activated. However, the internal wiring of the electrode leads will be disconnected to ensure that no electrical current is delivered to the non-acupoints.

By using non-meridian, non-acupoint locations and superficial, non-manipulated needling, we aimed to minimize acupoint-specific effects while maintaining credibility, in line with current recommendations for sham acupuncture controls (27, 28). Nonetheless, we acknowledge that even superficial needle insertion and cutaneous stimulation may elicit non-specific sensory or segmental neuromodulatory effects, so any between-group differences are likely to represent conservative estimates of the specific effects of EA.

All treatments will be administered by physicians and therapists, who will receive protocol-specific training. Before trial initiation, they will attend a structured workshop based on a written treatment manual detailing acupoint location, needling depth and angle, manipulation, stimulation parameters, and session duration for both EA and sEA. Adherence to the protocol will be monitored via treatment logs and periodic supervision to ensure consistency across practitioners.

### Safety evaluation

Safety monitoring will focus on adverse events (AEs) related to EA, including vasovagal reactions (dizziness, nausea, pallor, transient hypotension or syncope), intolerable needling pain, local hematoma or bruising, bleeding, infection or abscess at needle sites, needle breakage, and other post-needling reactions. All AEs will be recorded on standardized case report forms, noting the onset of time, duration, severity, relationship to the intervention, actions taken, and outcome. Serious adverse events (SAEs) will be defined according to Good Clinical Practice. Participants with repeated vasovagal episodes, severe AEs, or any SAE judged related to the intervention will discontinue study treatment and may be withdrawn if further participation is unsafe. All SAEs will be reported to the principal investigator and the institutional ethics committee within 24 h and will be managed according to the Data and Safety Monitoring procedures of West China Hospital.

### Outcome measures

#### Primary outcome measurement

The primary outcome is the change in MoCA scores from baseline to the end of the 4-week treatment period. This time point corresponds to completion of the EA course and the early subacute rehabilitation phase, when treatment intensity and neuroplastic potential are highest and short-term clinical decision-making is often made. MoCA is a validated screening tool for global cognitive function, covering seven domains: visuospatial/executive function, naming, attention, language, abstraction, delayed recall, and orientation (total score = 30). Using the standardized cutoff of <26 established for cognitive impairment detection, lower scores denote greater severity of cognitive dysfunction (29). To address longer-term clinical relevance, MoCA will also be reassessed at 3 months after stroke onset, and PSCI incidence at 3 months will be analyzed as a key secondary outcome.

#### Secondary outcomes

##### Cognitive function

The Mini-Mental State Examination (MMSE) will be used to assess global cognition. This 30-item scale evaluates seven domains: temporal orientation, spatial orientation, immediate recall, attention and calculation, delayed recall, language, and visuospatial abilities. Education-adjusted cutoff scores for cognitive impairment are: ≤17 for illiterate individuals, ≤20 for primary school, and ≤24 for junior secondary education or above (30).

##### Activities of daily living

Functional independence will be measured using the Modified Barthel Index (MBI), which assesses 10 daily activities (e.g., feeding, bathing, and mobility). Total scores range from 0 to 100, with lower scores indicating greater dependency (31).

##### Anxiety

Anxiety will be assessed using the Hamilton Anxiety Rating Scale (HAMA-14), which comprises 14 items divided equally into somatic anxiety and psychic anxiety. A total score ≥7 indicates probable clinical anxiety, while <7 falls within the normal range, with higher scores reflecting greater severity (32).

##### Depression

Depressive symptoms were evaluated via the 17-item Hamilton Depression Rating Scale (HAMD-17), covering seven domains: anxiety/somatization, weight changes, cognitive impairment, diurnal variation, psychomotor retardation, sleep disturbances, and hopelessness. Scores ≥7 suggest possible depression (<7 = normal), where elevated scores denote increased depressive severity (33).

##### Sleep quality

The Pittsburgh Sleep Quality Index (PSQI) will be used to evaluate subjective sleep quality over the past month. The index includes seven components scored from 0 to 3, producing a global score ranging from 0 to 21. Higher scores reflect poorer sleep quality (34).

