#### Inclusion criteria

Inclusion criteria include:

Meets both stroke and cognitive impairment definitions;Aged 18–75 years, either of sex;Ischemic stroke onset 7–30 days before enrolment;MoCA < 26 and able to cooperate with acupuncture and assessments;Stable vital signs;National Institutes of Health Stroke Scale (NIHSS) score 1–15;Written informed consent from the patient or legal guardian.

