#### Assessment timepoints

The primary outcome (MoCA) and most secondary outcomes (MMSE, MBI, HAMA, HAMD, and PSQI) will be assessed twice: at baseline and at the end of the 4-week treatment period. PSCI incidence, defined based on MoCA <26, will be assessed once at 3 months after stroke onset.

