Continuous variables will be presented as mean ± standard deviation (SD) when normally distributed or median with an interquartile range (IQR) for non-normally distributed data. Between-group comparisons will utilize independent samples t-tests for normally distributed variables and Mann–Whitney U-tests otherwise. Within-group pre-post comparisons will use the Wilcoxon signed-rank test. Correlation analyses will preferentially apply Pearson’s method; if either variable violates normality, Spearman’s rank correlation will be substituted. To control for confounders, covariates including age, sex, education level, stroke severity (baseline NIHSS score), and time from stroke onset to enrolment will be incorporated into multivariable linear regression models to evaluate between-group differences in the primary endpoint and key secondary cognitive outcomes. Where available, additional vascular and imaging-related factors, such as stroke subtype, lesion side, and vascular territory, lesion volume, baseline white matter hyperintensity burden (e.g., Fazekas score), receipt of intravenous thrombolysis, and major vascular comorbidities, will be explored as candidate covariates in sensitivity analyses.

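### For nearly all permitted entry days the baseline PSQI reaches back before the stroke, so PSQI change in the QSM correlations and any within-group test is not purely post-stroke change

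*Protocol article*

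**What the plan says.** All references are to the protocol article.

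- **Recall period** (Sleep quality): "The Pittsburgh Sleep Quality Index (PSQI) will be used to evaluate subjective sleep quality over the past month".
- **Entry window** (Inclusion criteria): "Ischemic stroke onset 7–30 days before enrolment".
- **Visits** (Assessment timepoints): PSQI is among the outcomes that "will be assessed twice: at baseline and at the end of the 4-week treatment period".
- **Order of events** (Randomization and blinding): "After confirming eligibility and completing baseline assessments, the treating acupuncturist will open the next envelope in sequence". Baseline PSQI is therefore recorded before allocation is known.
- **Clinical analysis** (Clinical data analysis): "Within-group pre-post comparisons will use the Wilcoxon signed-rank test". This is a general rule; it neither names nor excludes PSQI. For the arms, "Between-group comparisons will utilize independent samples t-tests for normally distributed variables and Mann–Whitney U-tests otherwise", without saying whether the PSQI variable is the week-4 score or the change. Time from onset is a regression covariate for the primary endpoint and the key secondary cognitive outcomes, so not for PSQI.
- **Imaging analysis** (Neuroimaging data analysis): Pearson or Spearman correlations will examine "associations between changes in ROI-based susceptibility and corresponding changes in cognitive, functional, emotional, and sleep measures". No adjustment is stated for them.

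Nothing in the article limits baseline recall to the time since the stroke, or says that pre-stroke sleep is the intended reference.

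**The concern.** A change from baseline can be read as post-stroke change only if both measurements describe the post-stroke period. Here the first usually describes a blend of sleep before and after the stroke, and the second describes post-stroke sleep only. A patient who slept well before the stroke could appear to worsen by week 4 even though sleep had improved since the stroke.

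The blend also differs between patients, because it depends on how many days after onset each one enters. That matters most for the imaging correlations. The Discussion describes iron deposition after stroke as progressive, so time from onset may also relate to susceptibility change over the following 4 weeks. If it does, an association between sleep change and iron change could appear, or be hidden, for reasons unrelated to sleep recovery. These estimates are meant to guide later trials, so it is worth knowing what they measure.

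**Working it through.** The plan gives no figure that depends on PSQI, so there is none to reproduce. The check is how far each recall window overlaps the time before the stroke.

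**Inputs.** d = days from onset to baseline, 7 to 30 (Inclusion criteria), taking baseline to fall at enrolment. M = length of the recall month. The article gives no number of days, so M = 28, 30 and 31 are used as an assumption. Treatment lasts 4 weeks = 28 days (Intervention and grouping).

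**Baseline window.** Pre-stroke share p = max(0, M − d)/M.

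| Entry day d | M = 28 | M = 30 | M = 31 |
|---|---|---|---|
| 7 | 21/28 = 75% | 23/30 = 77% | 24/31 = 77% |
| 14 | 14/28 = 50% | 16/30 = 53% | 17/31 = 55% |
| 21 | 7/28 = 25% | 9/30 = 30% | 10/31 = 32% |
| 30 | 0% | 0% | 1/31 = 3% |

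There are 30 − 7 + 1 = 24 permitted entry days. Some pre-stroke time remains in the window on 21 of them (M = 28), 23 (M = 30) or 24 (M = 31).

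**Average share if entry is uniform over days 7–30 (assumption).**
- M = 28: pre-stroke days sum to 21 + 20 + … + 1 = 231; 231/24 = 9.625; 9.625/28 = 34%.
- M = 30: 23 + 22 + … + 1 = 276; 276/24 = 11.5; 11.5/30 = 38%.
- M = 31: 24 + 23 + … + 1 = 300; 300/24 = 12.5; 12.5/31 = 40%.

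**If entry is late (assumption: 75% on days 21–30, 25% on days 7–20, uniform within each).**
- M = 28: baselines with some pre-stroke time = 0.25 + 0.75 × 7/10 = 78%. Mean share = (0.25 × 14.5 + 0.75 × 2.8)/28 = 5.725/28 = 20%.
- M = 30: 0.25 + 0.75 × 9/10 = 93%. Mean share = (0.25 × 16.5 + 0.75 × 4.5)/30 = 7.5/30 = 25%.

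**Week-4 window.** The earliest week-4 visit is on day 7 + 28 = 35 after onset. Even a 31-day window then starts on day 35 − 31 = 4 after onset, so it holds no pre-stroke days.

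**What this does to a change score.** As a simplification, suppose the baseline score weights days equally. Let P be the pre-stroke sleep score, S the post-stroke score at entry and W the week-4 score. Baseline = pP + (1 − p)S, and the change is

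W − baseline = (W − S) + p(S − P).

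The first term is post-stroke change. The second is the effect of the stroke itself, scaled by p. It vanishes if the stroke did not alter sleep (S = P) or if p = 0. Otherwise it varies with entry day. The article gives no values for P, S or W, so its size in PSQI points cannot be stated.

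**The case against.** Several stronger readings are tempting, and the article does not support them.

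- **That every PSQI analysis uses change scores.** Only the imaging correlations name change in sleep measures. The pre-post rule is general and does not mention PSQI, and the between-arm PSQI variable is not specified. A comparison of week-4 scores would be consistent with the text.
- **That the treatment comparison is biased.** It is not. Baseline is taken before allocation, so the overlap with pre-stroke time is the same in both arms in expectation. If change scores were used, the cost would be precision, and that loss cannot be put in figures from the article.
- **That 77% or 38% measures the distortion of the score.** These are shares of calendar days. Nothing shows that patients weight the days equally, and the averages depend on an entry distribution the article does not give.
- **That the sleep–iron correlation will be spurious.** A shared dependence on time from onset is plausible but not shown, because no rate of iron change by entry day is given. Confounding by time from onset could also affect the cognitive, functional and mood correlations. What is particular to PSQI is a recall window that crosses the stroke.
- **That the recall period should be shortened.** That would alter the instrument, and analysis changes can handle the mismatch.

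It is also fair to say that PSQI is one of several secondary outcomes declared exploratory, with descriptive p-values, and that all imaging findings are exploratory as well. The primary endpoint and sample size do not depend on PSQI. This limits the weight of the point. It does not change what the baseline score describes, and no passage corrects the mismatch.

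**Conclusion.** The point holds within limits. A past-month baseline includes pre-stroke time on 21 to 24 of the 24 permitted entry days, against none at week 4. That count rests only on the entry window, the visit schedule and a month of 28 to 31 days. The claim that most patients are affected further assumes that entry is not concentrated on days 28–30, and it survives the late-entry scenario.

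The consequence is confined to the sleep-change correlations with QSM change and to any within-group PSQI test run under the general rule. It is a matter of interpretation in exploratory analyses, but it is worth correcting because the correction uses only planned data.

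**What to change.** 1. **Between arms:** compare week-4 PSQI, with baseline PSQI and time from onset as covariates. Baseline PSQI remains a valid covariate because it precedes allocation, whatever period it describes.
2. **Within group:** exclude PSQI from the pre-post tests.
3. **Imaging correlations:** either drop the PSQI change correlation, or correlate QSM change with week-4 PSQI adjusted for time from onset.
4. **Wording:** state under Sleep quality that baseline PSQI partly reflects pre-stroke sleep, to an extent that depends on time from onset.

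PSQI is already scheduled at both visits and time from onset is already a listed covariate, so no new data are needed. The cost is a change of wording and one altered exploratory analysis. Leave the PSQI recall period unchanged.
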